## Study design

This is a prospective, multicentre, randomized, assessor-masked, 3-arm (1:1:1), active-controlled trial of 360 subjects with meibomian gland dysfunction contributing one study eye. For subjects with both eyes eligible, the eye with the most meibomian gland dropout (meiboscore), fewest expressible meibomian glands, thinnest lipid layer, or lowest TFBUT values (in this order) will be selected as the study eye.

Enrolled patients will be randomized into one of the following groups, 1 month after recruitment during the 15-month study period receiving bilateral treatment of:

Group A: 1-session VTP at month 0

Group B: 4-session IPL+MGX at month 0,1,2,3

Group C: twice daily EW for 15 months

The study will be conducted in accordance with the tenets of the Declaration of Helsinki, and the protocol will be sent for approval by the research ethics review committee of each participating hospital. All participants will provide written informed consent before participation. Study will be registered at ClinicalTrials.gov prior to recruitment. The baseline, follow-up assessments and study procedures will be conducted as described above. Participants will be given contact of the study team to report adverse events at any time, which will also be actively sought at each follow-up visit. Additional follow-up appointment will be provided as and when required.

Recruitment, baseline and follow-up assessment and tear substitutes

Patients will be washed out for 1 month and maintained on one single topical lubricant to be used as frequently as needed from recruitment to study exit (total 16 months). Cool Eye eye drops- hypromellose (3 mg/ml) containing 0.0002 ml of 50% Benzalkonium Chloride solution as preservative will be provided by the research team.

Clinical evaluations are done according to the recommendations of the TFOS DEWS II diagnostic methodology subcommittee at month -1 (recruitment), 0 (baseline), 1, 2, 3, 4, 6, 9, 12, 15 (total 10 visits). Examination is conducted on both eyes starting on the study eye. To minimize the impact on ocular surface and tear film physiology, tests are done from least to most invasive at each follow-up and/or prior to each treatment.

Randomization, masking of assessors

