## Data processing and analysis

Trial biostatistician will oversee data acquisition, processing and statistical analysis.

Record keeping, confidentiality and monitoring

A unique study number will be assigned to each recruited subject for all study-related documents. The log containing study number to identifiable information will be kept in a locked cabin at the clinical trial office at CUHKEC. All trial-related documents will be maintained by the unmasked trial coordinator to ensure data are accurate, complete, and verifiable from case report forms. Data entry will be cross-checked by a designated technician.

**Primary outcome**: Tear film breakup time (TFBUT) at month 6, month 15

**Secondary outcomes**: Serial measurements of MG, tear-film related parameters, intraocular pressure, compliance to EW, factors associated with MGD outcomes and treatment related complications.

Sample size calculation

Based on Arita et al for IPL+MGX[23] and Lane et al for VTP[24], the estimate mean differences in changes of TFBUT are 3.3 for IPL+MGX and 1.9 for VTP, the pool estimates of SDs are 1.88 for IPL+MGX and 4.04 for VTP. Given a 2.5% type I error (Bonferroni correction) and assuming an average SD of 3, a minimum sample of 88 patients per group can detect a significance difference in change of TFBUT between groups. By assuming a 35% of drop-out over an extended study period (16 months from recruitment), 120 subjects per group are required. This sample size is powered to detect differences between VTP and EW or between IPL and EW given the estimates of EW from Lane et al.

Statistical analysis

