The intention-to-treat principle will be applied during the data analysis using Graph Pad Prism version 8.01 (California, USA) and IBM SPSS version 24 (New York, USA) and reported according to CONSORT guidelines for RCT. Categorical data at baseline are analysed using chi-squared or Fisher’s exact tests. Data are presented as mean± SD, or median (IQR) unless otherwise stated. Study outcomes will be compared between groups using pair-wise t-test. Continuity-adjusted chi-squared testing will be applied to compare proportion of patients between treatment arms on secondary outcome. Further comparisons of the primary and secondary outcomes between treatment arms, at baseline and pre-set intervals will be made using risk ratio (RR) for dichotomous data and mean difference for continuous data with 95% confidence interval. Appropriate (logistic or linear) regression models, adjusting for minimisation and outcome variables at baseline will be computed for prognostic factors. Multivariate analyses will be conducted to control with baseline measurements, covariates, and repeated measurements. Correlations between parametric and nonparametric data are assessed with Pearson product-moment correlation or Spearman rank order correlation, respectively. The proportions of eyes developing complications during and after the procedures are compared with Chi-square test. All tests are two-tailed, and p<0.05 is considered significant.

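### Complications are to be compared per eye with a plain chi-square test, although patients are randomised and both eyes are treated; a patient-level rule also covers them, so the unit of the safety comparison is unsettled

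*Protocol*

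**What the plan says.** Under Statistical analysis the protocol fixes both unit and test for complications: "The proportions of eyes developing complications during and after the procedures are compared with Chi-square test". The section closes with "All tests are two-tailed, and p<0.05 is considered significant".

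Four other statements bear on the unit:

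- Study design has each subject "contributing one study eye" and gives an ordered rule for choosing it when both eyes qualify.
- Study design also has every randomised patient "receiving bilateral treatment of" the assigned therapy, and adds: "Examination is conducted on both eyes starting on the study eye".
- Statistical analysis has a separate rule for secondary outcomes expressed as proportions: "Continuity-adjusted chi-squared testing will be applied to compare proportion of patients between treatment arms on secondary outcome".
- The list of secondary outcomes ends with "factors associated with MGD outcomes and treatment related complications".

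The safety block of the Study Table contains eye measures (for example lens opacity and iris defects) and also facial redness, swelling, bruises and pigmentation.

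**The concern.** Allocation is by patient, so the patient is the independent unit. Two eyes of one patient share the therapy, the operator, the skin type and the healing response, and their complications will tend to occur together. A Pearson chi-square test on eyes assumes that every eye is independent. If both eyes enter, it overstates the amount of information.

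If the sentence means study eyes only, that problem disappears and another takes its place: the fellow eye receives the same treatment and is examined at the same visits, but its complications do not enter the comparison. The facial items fit neither count, because they are not events of an eye.

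Complications also appear to fall under two rules that differ in unit (eye or patient) and in test (plain or continuity-adjusted). An analyst could follow either after seeing the data. Safety stands beside efficacy in the Primary Objective, so its comparison should have one defined unit.

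**Working it through.** **Inputs from the protocol.** Three arms, 1:1:1, 120 patients per arm (240 eyes per arm if both are counted); two-sided 5% level. The protocol gives no complication rate and no between-eye correlation (rho), so both are assumed below and shown over a range.

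**Reproducing the stated level.** With one eye per patient, or rho = 0, the formulas below return 0.05, the level the protocol states.

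**Both eyes counted.** For clusters of two, the variance is (1 + rho) times what the test assumes.

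- Two arms: true error = 2 × [1 − Φ(1.96 / √(1 + rho))]
- Three arms (2 df): true error = P(χ²₂ > 5.99 / (1 + rho))
- Independent eyes that 240 eyes are worth: 240 / (1 + rho)

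| rho (assumed) | Two arms | Three arms | Effective eyes per arm |
|---|---|---|---|
| 0 | 0.050 | 0.050 | 240 |
| 0.2 | 0.074 | 0.082 | 200 |
| 0.5 | 0.110 | 0.136 | 160 |
| 0.8 | 0.144 | 0.189 | 133 |
| 1.0 | 0.166 | 0.224 | 120 |

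Example at rho = 0.5: 1.96 / √1.5 = 1.600, and the two-sided tail area is 0.110.

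The error reaches 10% when 1.96 / √(1 + rho) = 1.645, that is 1 + rho = (1.96 / 1.645)² = 1.42, so rho is about 0.42. For three arms it takes about 0.30.

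**Simulation check.** With 120 patients per arm, 40,000 replicates and complication rates of 2%, 5% and 10%, the two-arm error was 0.068 to 0.074 at rho 0.2, 0.109 to 0.110 at rho 0.5 and 0.141 to 0.153 at rho 0.8. A continuity correction applied to eye counts at rho 0.5 gave 0.056 to 0.086, which is less inflated but still above 5%.

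**Study eye only.** The error stays at 0.05, but 120 of the 240 treated eyes per arm leave the comparison. To illustrate, take an assumed rate p = 5% in each eye. The probability that both eyes are affected is p² + rho × p(1 − p).

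- At rho 0.5: both eyes 0.0025 + 0.5 × 0.0475 = 0.0263; at least one eye 0.10 − 0.0263 = 0.0738; fellow eye only 0.05 − 0.0263 = 0.0238. The share of affected patients not counted is 0.0238 / 0.0738 = 32%.
- At rho 0.2: 0.038 / 0.088 = 43%.
- At rho 0.8: 0.0095 / 0.0595 = 16%.

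**The case against.** The strongest reply is that the protocol never says both eyes enter the test. Study design speaks of one study eye per subject, and examining both eyes describes data collection, not the unit of analysis. If the sentence means study eyes, the test holds its level. This stands: inflation is conditional and cannot be asserted as fact. It does not settle the matter, because the same section writes of patients for secondary outcomes and of eyes for complications. With one eye per patient the change of word would have no purpose.

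A second reply is that a patient-level test, and risk ratios with 95% CI for dichotomous outcomes, are already planned. That is right, and much of the remedy is therefore already in the document. But the eye-level sentence is the specific one and stands beside the general rule without reference to it. Nor does the general provision for repeated measurements mention fellow eyes or complications.

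Three stronger readings are tempting and are not supported:

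- A reader might infer that the error rate roughly doubles. That needs rho near 0.42 for two arms, and the protocol gives no correlation.
- A reader might infer that fellow-eye complications go unrecorded. Both eyes are examined; only the formal comparison would omit them.
- A reader might infer that Fisher's exact test is barred for complications. It is named for baseline data, but nothing excludes it elsewhere, and a fallback for sparse tables is ordinary detail for an SAP, which is not at hand.

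It is also fair to say that an anti-conservative safety test tends to flag too many differences and does not hide them.

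**Conclusion.** The point holds as a defect in a stated rule. The protocol names a unit and a test that fit the design poorly on either reading, and a second rule with a different unit also covers the outcome. This is not detail left to an SAP, since an SAP would have to override or reinterpret the sentence.

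The size depends on the reading. With both eyes counted, a nominal 5% two-arm test runs at about 7% to 14% for an assumed rho of 0.2 to 0.8, and a three-arm test at about 8% to 19%. With study eyes only, the level is correct, but the fellow eye's complications are left out; the share of affected patients missed depends on an assumed rate and correlation.

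The consequence is confined to the comparison of complications. The primary TFBUT analysis and the sample size do not depend on it.

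**What to change.** Replace the eye-level sentence under Statistical analysis with one rule: the proportion of patients with at least one treatment-related complication in either eye or in the periocular or facial skin, compared between arms by a single named test (exact when counts are sparse), reported with a risk difference or risk ratio and its 95% CI. State that this rule, and not the general one for secondary outcomes, governs complications. If eye-level rates are also tested, use GEE or a cluster-robust variance with the patient as cluster.

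The cost is a change of wording. Both eyes and the face are already assessed, so no new data are needed. Intervals will be somewhat wider than a naive count of both eyes would give.

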# Aims and hypotheses to be tested

Primary Objective

To compare the efficacy and safety of 1-session vectored thermal pulsation (VTP) or 4-session intense pulsed light and meibomian gland expression (IPL+MGX) with twice-daily eyelid warm compress (EW) therapy for meibomian gland dysfunction (MGD)

Secondary Objectives

1. To compare the course of MGD among groups over 15 months (12-month after final IPL+MGX)
2. To identify factors predicting responses and compliance to therapies

Hypotheses

1. Both 1-session VTP and 4-session IPL+MGX are more efficacious than twice-daily EW in improving MGD
2. MGD improves earlier after VTP
3. MGD improvement lasts longer after 4-session IPL+MGX

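### Hypotheses 2 and 3 have no outcome, contrast or visit attached, and one blanket p<0.05 rule covers every test that could be cited for them

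*Protocol*

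**What the plan says.** Under Aims and hypotheses to be tested, the protocol gives an onset hypothesis, "MGD improves earlier after VTP", and a duration hypothesis, "MGD improvement lasts longer after 4-session IPL+MGX". The Introduction counts onset, offset and time course among the knowledge gaps that the trial is meant to close.

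Under Data processing and analysis, the primary outcome is TFBUT at months 6 and 15. The secondary outcomes form one unranked group: "Serial measurements of MG, tear-film related parameters, intraocular pressure, compliance to EW, factors associated with MGD outcomes and treatment related complications".

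The Statistical analysis text then provides for:
- pair-wise t-tests of the study outcomes between groups, with no visit named;
- "Further comparisons of the primary and secondary outcomes between treatment arms, at baseline and pre-set intervals will be made", expressed as risk ratios or mean differences with 95% confidence intervals;
- multivariate analyses that allow for repeated measurements, without a model or a target contrast;
- a closing rule for everything: "All tests are two-tailed, and p<0.05 is considered significant".

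The one multiplicity adjustment is in the sample size calculation: "Given a 2.5% type I error (Bonferroni correction) and assuming an average SD of 3, a minimum sample of 88 patients per group". That text describes the powered contrasts as VTP against EW and IPL against EW.

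**The concern.** The onset and duration statements are presented as hypotheses to be tested, so readers of the trial report will expect a yes or no on each. The protocol does not say what would count as a yes. Earlier or longer than which arm, on which measure and at which visit are all open. The text that does apply calls every result with p<0.05 significant.

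Followed as written, nothing stops any one measure at any early visit from being reported as confirming hypothesis 2, or any one measure at a late visit as confirming hypothesis 3. Different measures or visits could support opposite conclusions. What is at stake is the credibility of the two claims that distinguish VTP from IPL+MGX. The comparison of each with EW is a separate matter.

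**Working it through.** **1. The plan's own figure.** The only place where the protocol adjusts for multiplicity is the sample size. Inputs: "the estimate mean differences in changes of TFBUT are 3.3 for IPL+MGX and 1.9 for VTP"; standard deviations of 1.88 (IPL+MGX) and 4.04 (VTP), averaged to 3; two-sided alpha 0.025. Power is not stated, so 80% is assumed.

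n per group = 2 × (z₀.₉₈₇₅ + z₀.₈₀)² × SD² / δ² = 2 × (2.241 + 0.842)² × 9 / δ²

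| δ | n per group |
|---|---|
| 3.3 − 1.9 = 1.4 | 87.3, rounded up to 88 |
| 1.9 | 47.4, rounded up to 48 |
| 3.3 | 15.7, rounded up to 16 |

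The stated 88 is reproduced at the 2.5% level, but only with the difference between the two active arms. The text names the contrasts with EW, and that mismatch is a separate matter. For this point, the 2.5% is a planning level. The analysis text neither repeats it nor assigns any of it to hypotheses 2 and 3.

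**2. Size of the secondary family.** The protocol gives no count, so three are used:
- Narrow: 12 outcomes from the Study Table (6 meibomian gland, 5 tear film, intraocular pressure).
- Objective: the 17 objective efficacy rows other than TFBUT.
- Broad: 23 outcomes (the 17, five symptom scales, intraocular pressure).

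There are 8 post-baseline visits (months 1, 2, 3, 4, 6, 9, 12, 15) and 3 arm pairs. Visit by visit:
- 12 × 8 × 3 = 288 tests; × 0.05 = 14.4 false positives expected
- 17 × 8 × 3 = 408 tests; × 0.05 = 20.4 expected
- 23 × 8 × 3 = 552 tests; × 0.05 = 27.6 expected

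**3. Chance of at least one false positive with no true difference.** Simulated trials draw three arm means for every outcome and visit, with exchangeable correlation between outcomes and between visits. Each pair is tested by z = (difference in arm means)/√2, significant if |z| > 1.96. All correlations are assumptions.

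| Family | Correlation between outcomes / visits | Chance |
|---|---|---|
| 12 outcomes, each visit | 0.3 / 0.5 | 99.8% |
| 12 outcomes, each visit | 0.5 / 0.7 | 98.0% |
| 12 outcomes, each visit | 0.5 / 0.9 | 88.6% |
| 12 outcomes, each visit | 0.7 / 0.9 | 76.1% |
| 17 outcomes, each visit | 0.5 / 0.5 | 99.9% |
| 17 outcomes, each visit | 0.7 / 0.7 | 95% |
| 17 outcomes, each visit | 0.8 / 0.8 | 82–83% |
| 12 outcomes, one repeated-measures result each (36 tests) | 0.7 down to 0 between outcomes | 47–79% |
| 23 outcomes, one repeated-measures result each (69 tests) | 0.7 down to 0 between outcomes | 58–95% |

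**4. Hypotheses 2 and 3 directly.** Assumed reading: a significant result in the hypothesised direction on any of 18 measures (the 17 plus TFBUT) counts as support. The comparison is VTP against IPL+MGX. Early means months 1 to 4 and late means months 9, 12 and 15.

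| Correlation | Hypothesis 2 (18 × 4 = 72 chances) | Hypothesis 3 (18 × 3 = 54 chances) |
|---|---|---|
| 0.3 / 0.5 | 58% | 51% |
| 0.5 / 0.5 | 46% | 40% |
| 0.8 / 0.8 | 21% | 19% |

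One named contrast, tested two-sided at 0.05 and counted in one direction, gives 0.05 / 2 = 2.5%. If VTP better than EW may also count for hypothesis 2, the range is 34% to 77%.

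**5. What a fix achieves.** Two named tests, each at 0.05, unadjusted and independent, would give 1 − 0.95² = 9.75%. A fixed order holds that pair at 5% or less. Bonferroni over 288 tests would need 0.05 / 288 = 0.00017 per test, which is why a short list is the workable route.

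**The case against.** The strongest reply is that ordering secondary outcomes and defining the contrast for a secondary hypothesis are usual content of an analysis plan, which is not at hand. That stands as far as mere silence goes. Here, though, the protocol is not silent. It calls these hypotheses to be tested and then fixes a significance rule for all tests. An analysis plan that set a hierarchy or an exploratory label would have to depart from that sentence.

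A reader might infer that hypotheses 2 and 3 are to be tested pair-wise at every visit, and that a false significant result is then almost certain. The documents do not support either step:
- No test is assigned to these hypotheses. The pair-wise t-test sentence names no visits. The sentence about pre-set intervals describes estimates with 95% confidence intervals.
- A repeated-measures analysis is planned, which would give far fewer results per outcome.
- The test counts, the correlations and the rule that any measure at any visit suffices are assumptions. At high correlation the chance falls to about 76% to 83%.

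These points limit the size of the problem without removing it. A 95% interval that excludes no difference corresponds to p<0.05, so the blanket rule reaches the interval comparisons too. The repeated-measures analysis is unspecified and is not named as the deciding one. Even one result per outcome and contrast leaves 47% to 95%.

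The same p<0.05 sentence also sits badly with the 2.5% level in the sample size. That bears on the primary comparisons and is a different point.

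**Conclusion.** The point holds in a limited form. Two stated hypotheses have no defined outcome, contrast, visit or test, and the rule they fall under offers no error control. If any measure at any early or late visit may serve as support, the chance of a false supporting result is roughly 20% to 60% for hypothesis 2 and 20% to 50% for hypothesis 3, against 2.5% for one named contrast. For the secondary outcomes as a whole, at least one false positive is very likely if they are tested visit by visit (about 76% to over 99%, for 12 or 17 outcomes). It remains substantial under a repeated-measures analysis (about 47% to 95%, for 12 to 23 outcomes).

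The gap in definition and the blanket rule are on the face of the protocol. The percentages depend on assumed correlations, assumed outcome counts and an assumed reading of what counts as support. Correcting this is a cheap improvement. It does not challenge the design or the two comparisons with EW.

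**What to change.** In Aims and hypotheses to be tested, and in the outcome and Statistical analysis text of Data processing and analysis:
1. For each of hypotheses 2 and 3, name one outcome, one arm contrast and one visit, or one repeated-measures contrast. The sponsor should choose the outcome and visit.
2. Test the two in a pre-stated order, after the primary contrasts with EW have succeeded at their controlled level.
3. Limit the p<0.05 significance sentence to that ordered list.
4. Report all other secondary outcomes, visits, arm pairs and predictor analyses as exploratory estimates with 95% confidence intervals, without significance claims.

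The cost is a few sentences, with no extra patients or data. The small downside is that an isolated secondary result with p<0.05 can no longer be presented as confirmed.

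### The trial is sized at a Bonferroni 2.5% per comparison but analysed at p<0.05 throughout, giving about 9% family-wise error for the two comparisons with EW at a single month, with no rule for the two primary months

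*Protocol*

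**What the plan says.** All the statements on error rate stand in the protocol under Data processing and analysis.

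- **Primary outcome:** "Tear film breakup time (TFBUT) at month 6, month 15". The Study Table marks TFBUT as primary at the same two visits.
- **Sample size calculation:** "Given a 2.5% type I error (Bonferroni correction) and assuming an average SD of 3", leading to 88 patients per group. The comparisons covered are named: "This sample size is powered to detect differences between VTP and EW or between IPL and EW".
- **Statistical analysis:** "Study outcomes will be compared between groups using pair-wise t-test". Mean differences for primary and secondary outcomes are to carry 95% confidence intervals. The paragraph ends: "All tests are two-tailed, and p<0.05 is considered significant".

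The primary objective, under Aims and hypotheses to be tested, likewise compares each active treatment with EW. The protocol gives no order of testing, no split of alpha over months 6 and 15, and no requirement that both months be significant.

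**The concern.** The sample size section treats the two comparisons with EW as a family and divides 5% by two. The analysis section then tests each at the full 5%, so the two sections cannot both govern the primary analysis. Followed as written, the analysis would support a superiority claim at a looser error rate than the one on which the trial was sized.

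The two primary months add a second problem. Two comparisons at two months make four primary tests, while the 2.5% level allows for two. If the threshold or the month that counts is chosen after results by arm are known, the choice is post hoc.

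**Working it through.** **1. Is the 2.5% a two-sided Bonferroni level?**

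The protocol gives effects of 3.3 (IPL+MGX) and 1.9 (VTP) and an average SD of 3. It states neither the power nor the difference used. Assume 80% power and a difference of 3.3 − 1.9 = 1.4.

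n per group = 2 × (z for alpha + z for power)² × SD² / difference²

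- Two-sided 0.025: 2 × (2.2414 + 0.8416)² × 9 / 1.96 = 87.3, so **88**, the stated figure.
- Two-sided 0.05 (the same as one-sided 0.025): 2 × (1.9600 + 0.8416)² × 9 / 1.96 = 72.1, so 73.

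On these assumptions the stated 88 needs two-sided 0.025. Another route (difference 1.9, SD 4.04, two-sided 0.025, 80% power) gives 86, which is close but not exact.

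**2. Family-wise error for the two comparisons with EW at one month**

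With 1:1:1 allocation and a shared EW arm, the two test statistics have correlation 0.5. If neither active arm differs from EW:

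- each at 0.05: **9.1%** (independent tests would give 1 − 0.95² = 9.75%);
- each at 0.025: 4.7%.

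**3. The same two comparisons at months 6 and 15, a rejection at either month counting**

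The within-patient correlation of TFBUT between the two months is not given and is assumed. The figures come from 2 million simulated draws of three arms' means at two months, with no difference between arms at either month.

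| Month 6/15 correlation | Four tests at 0.05 | Four tests at 0.025 | Four tests at 0.0125 |
|---|---|---|---|
| 0.3 | 16.9% | 8.9% | 4.6% |
| 0.5 | 16.1% | 8.5% | 4.4% |
| 0.7 | 14.9% | 7.9% | 4.1% |
| 0.9 | 12.6% | 6.7% | 3.5% |

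Four independent tests at 0.05 would give 1 − 0.95⁴ = 18.5%.

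**4. Other rules for the two months**

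- *Both months required, each at 0.05:* 0.5% (correlation 0) to 5.5% (correlation 0.9) when no arm has an effect at either month. If both active arms truly work at one month only, the rate of wrongly claiming both months moves up towards the single-month 9.1%.
- *Both months required, each at 0.025:* no more than the single-month 4.7%, because every claim needs a rejection at a month without an effect.
- *Month 6 first at 0.025, month 15 only if month 6 is significant:* about 4.6% to 4.7% when there is no effect anywhere, because any rejection needs one at month 6. Under any pattern of true effects the bound is 0.025 + 0.025 = 5%.

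**The case against.** **The 13% to 17% is not the size of the stated contradiction.** A reader might infer that the protocol's family-wise error simply is 13% to 17%. That needs an either-month success rule, which the protocol does not state, and an assumed correlation. This objection stands. The part that follows from the text is 0.025 in sizing against 0.05 in analysis, which is 9.1% at one month.

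**Sharing alpha over time points is commonly left to an SAP, and one may exist.** This stands in part. Silence about months 6 and 15 alone would be weak ground. A threshold stated for all tests is not silence, however; it is a fixed rule that conflicts with the sample size section.

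**The p<0.05 sentence may be only a general default, or refer to adjusted p-values.** The text supports neither. It exempts no outcome, mentions no adjusted p-values, and the 95% intervals cover the primary outcome. It does not follow that the sponsor meant to abandon the correction; an oversight is just as consistent with the text.

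**Six tests.** A reader might add IPL+MGX against VTP, since the tests are pair-wise, and reach 17% to 23%. The protocol does not support this. Its primary objective and its power statement name only comparisons with EW.

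**Direction.** The two-sided figures include false findings in favour of EW. Counting only false findings in favour of an active arm, the either-month rate at 0.05 is about 8.5% to 6.3%, against a matching benchmark of 2.5%. The inflation remains, but 13% to 17% should not be read as the chance of a false superiority claim.

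**Hypothesis 1 says both active treatments are better than EW.** If only that joint claim counted, no correction across arms would be needed. The protocol's own Bonferroni step points to separate claims, so this remains an alternative reading that the text does not adopt.

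**Conclusion.** The point holds as an internal contradiction. The sample size uses 2.5% per comparison with EW, while the analysis uses 5% and 95% intervals. For the two comparisons at one month, this raises the two-sided family-wise error from about 4.7% to about 9.1%. That result needs only equal allocation, a shared EW arm and approximately normal test statistics.

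The two primary months widen the problem conditionally. If a rejection at either month counts, the error is about 13% to 17% at 0.05 and still about 7% to 9% at 0.025, for an assumed correlation of 0.3 to 0.9. If both months were required, it would be 0.5% to 5.5% at 0.05 with no effect at either month. The protocol does not say which rule applies, so no single figure over both months can be attributed to it.

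**What to change.** For the primary outcome, replace the general p<0.05 rule with these statements:

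1. VTP against EW and IPL+MGX against EW are each tested at two-sided 0.025, with 97.5% confidence intervals.
2. The two months share that 0.025 by a named rule. For example, month 6 is tested first and month 15 only if month 6 is significant at 0.025. Alternatively, both months must be significant.
3. IPL+MGX against VTP and all other outcomes are secondary, with nominal p-values.

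The cost is a few sentences, settled before any results by arm are seen. The sizing alpha is kept, so the change of threshold adds no patients to the planned calculation.

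The choice of rule is the sponsor's, and each has a price. Under month 6 first, month 15 cannot be claimed for an arm that fails at month 6, which matters in a trial that stresses durability to 15 months. Requiring both months demands two significant results per arm. An equal split of 0.05/4 = 0.0125 per test also controls the error (3.5% to 4.6% in the table) and ranks the months equally. With a difference of 1.4, SD 3 and 80% power, however, it raises the requirement from 88 to 103 evaluable patients per group.
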